#### Physical activity levels

The Community Healthy Activities Model Program for Seniors (CHAMPS) physical activity survey will be used to assess participation in a comprehensive list of low, moderate and vigorous physical activities [68]. This questionnaire will provide valuable information about changes in physical function and physical activity behaviour over the course of the study.

#### Symptom related quality of life

The POS-S Renal questionnaire will be given to patients during the familiarisation session to assess their quality of life in direct relation to the symptoms experienced as a part of their condition [69]. This questionnaire provides valuable feedback about any changes experienced by patients regarding quality of life and disease-specific symptoms as a result of the intervention.

### Statistical analysis

All statistical analyses will be performed using SPSS 22.0 (IBM Corp, Chicago IL, United States of America). Participant characteristic and demographic data will be presented using descriptive statistics, and compared using independent t-tests for continuous variables and chi-square tests for categorical variables. The distribution of data will be assessed for normality with a Shapiro-Wilks test (*P* > 0.05). Non-normally distributed data will be compared using the Friedman non-parametric test. Otherwise, comparisons between groups for all continuous primary and secondary variables measured will be made using one-way analysis of variance (ANOVA). Main effects will be analysed using a Tukey post hoc test. A significance level of *P* < 0.05 will be adopted for all statistical tests. All data will be presented as means ± SEM unless stated.

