**Methods:**

This is a randomised controlled trial design. A total of 75 participants will be recruited from haemodialysis clinics. Participants will be allocated to a blood flow restriction cycling group, traditional cycling group or usual care control group. Both exercising groups will complete 3 months of cycling exercise, performed intradialytically, three times per week. The blood flow restriction cycling group will complete two 10-min cycling bouts separated by a 20-min rest at a subjective effort of 15 on a 6 to 20 rating scale. This will be done with pressurised cuffs fitted proximally on the active limbs during exercise at 50% of a pre-determined limb occlusion pressure. The traditional cycling group will perform a continuous 20-min bout of exercise at a subjective effort of 12 on the same subjective effort scale. These workloads and volumes are equivalent and allow for comparison of a common blood flow restriction aerobic exercise prescription and a traditional aerobic exercise prescription. The primary outcome measures are lower limb strength, assessed by a three repetition maximum leg extension test, as well as objective measures of physical function: six-minute walk test, 30-s sit to stand, and timed up and go. Secondary outcome measures include thigh muscle cross sectional area, body composition, routine pathology, quality of life, and physical activity engagement.

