Studies examining the haemodynamic responses to blood flow restriction identify blood flow restriction aerobic exercise training as having lower haemodynamic stress than high intensity resistance training, while providing similar outcomes [38–40]. As such, blood flow restriction is purported to be a potentially beneficial addition to exercise for clinical populations who may be contraindicated to high-intensity resistance training. While blood flow restriction exercise is a novel addition to exercise among ESKD patients, pilot data from this laboratory (unpublished) indicates that haemodynamic responses (systolic blood pressure, diastolic blood pressure, mean arterial pressure, heart rate) do not differ markedly between low-intensity blood flow restriction and non-blood flow restriction aerobic exercise both performed during haemodialysis in this population.

Aerobic capacity and muscle strength are both key physiological factors underpinning physical function [41] and both can improve with blood flow restriction aerobic exercise training. As declines in physical function, muscle strength, and aerobic capacity, as well as accelerated muscle atrophy are common among patients with ESKD, blood flow restriction aerobic exercise training may present an opportunity to increase the efficiency of time spent exercising for this population.

This study will examine the efficacy of blood flow restriction aerobic training among patients with ESKD on haemodialysis (HD). We hypothesise that blood flow restriction aerobic exercise training will improve physical function, muscle strength, and muscle size among patients with ESKD beyond that of traditional aerobic exercise training.

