### Sample size calculation

The most relevant outcome for blood flow restriction training studies is knee extensor muscle strength, and this was used as the main primary outcome measure for calculating required sample size. Based on data from previous blood flow restriction research [25, 29, 32, 33], and previous exercise for ESKD research [18, 42, 43], the projected percentage changes in knee extensor muscle strength for each of the three groups are CON = −3%, CYC = 2%, BFR-C = 12%. The common standard deviation within group, based on the prior research was determined to be 15. Thus, to achieve a power of 80% at an α level of 0.05, 20 participants per group will be required to detect a difference between the expected means for percentage strength improvement. However, based on previous work conducted by this research group a conservative attrition rate of 20% is expected over 3 months due to voluntary patient withdrawal, death, additional hospitalisation, transfer to another facility, or patients receiving transplants [23]. Thus, a total of 75 participants will be recruited and randomly allocated to one of the three groups.

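### A Shapiro-Wilk gate can send a primary outcome to a Friedman test, which does not compare three independent arms and has no BFR-C v CYC contrast

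*Protocol article*

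**What the plan says.** The Statistical analysis section sets a two-stage rule for continuous variables.

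- Stage one is a normality check with a 0.05 threshold: "The distribution of data will be assessed for normality with a Shapiro-Wilks test".
- If the check fails: "Non-normally distributed data will be compared using the Friedman non-parametric test". No pairwise follow-up is named for this branch.
- If it passes: "Otherwise, comparisons between groups for all continuous primary and secondary variables measured will be made using one-way analysis of variance (ANOVA"), followed by "Main effects will be analysed using a Tukey post hoc test". Tukey is the only pairwise procedure in the section.

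Three other places bear on the rule. The Background hypothesis is that BFR-C improves physical function, strength and "muscle size among patients with ESKD beyond that of traditional aerobic exercise training", so BFR-C v CYC is the comparison of interest. The abstract's Methods paragraph lists four primary outcomes: leg-extension strength and "objective measures of physical function: six-minute walk test, 30-s sit to stand, and timed up and go". The Sample size calculation is built on group means with a common SD: "20 participants per group will be required to detect a difference between the expected means for percentage strength improvement".

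**The concern.** The second branch opens on the result of a significance test on the outcome's own data, so the analysis a primary outcome receives is known only after its data are in. That would matter less if both branches answered the same question. Here they do not.

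- The Friedman test ranks values within blocks of related observations. The three arms are independent groups of different people. The only related observations in the main outcome data are baseline and 12 weeks, and a Friedman test on those would compare visits, not arms.
- Tukey belongs to the ANOVA branch. A switched outcome therefore has no stated BFR-C v CYC test.
- A switched outcome also leaves the difference in mean improvement, which is the quantity the trial was sized to detect. Because the gate works outcome by outcome, the four primary outcomes could end on different scales.

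At stake is whether the hypothesised comparison is produced at all for a given primary outcome. Ordinary sampling variation, or skew that ANOVA tolerates, could decide this.

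**Working it through.** **1. The plan's own figure.** Inputs from the Sample size calculation: means −3, 2 and 12 (per cent change), SD 15, α 0.05, 20 per group.

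- Grand mean = 11/3 = 3.667. Squared deviations are 44.44, 2.78 and 69.44, which sum to 116.67.
- Cohen's f = √(116.67/3)/15 = 0.416.
- Noncentrality at 20 per group = 20 × 116.67/225 = 10.37.
- Omnibus F-test power is 78.6% at 19 per group and 80.9% at 20. With 20% attrition, 60/(1 − 0.20) = 75.

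Both figures reproduce, and they belong to the ANOVA branch only.

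**2. How often exactly normal data are switched.** Each check rejects in about 5% of cases by construction.

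- One outcome, one check: about 5%. One outcome, each of three arms checked: 1 − 0.95³ = 14.3%.
- At least one of four outcomes, one check each, independent: 1 − 0.95⁴ = 18.5%. Simulated with correlation 0.5 between outcomes: 16.5%.
- At least one of four outcomes, checked by arm, all 12 checks independent: 1 − 0.95¹² = 46.0%.

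**3. What this does to BFR-C v CYC.** The simulation used 20 per arm and the plan's means and SD, with 20,000 runs for normal data and 6,000 for each skewed case. The Tukey contrast used q = 3.403 on 57 df. The skewed cases are lognormal errors scaled to SD 15. This is an assumption, because the protocol gives no distributional data. All entries are per cent; triplets are Shapiro-Wilk on pooled values / on residuals / in any arm.

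| Data | Outcome switched | Contrast significant if always run | Contrast reached and significant under the gate |
|---|---|---|---|
| Normal | 4.6 / 4.8 / 14.3 | 38.4 | 36.6 / 36.5 / 32.7 |
| Skewness 0.61 (CV about 0.2) | 26.5 / 32.6 / 36.5 | 39.2 | 28.1 / 27.6 / 25.9 |
| Skewness 0.95 (CV about 0.3) | 47.3 / 59.8 / 55.9 | 40.0 | 20.9 / 18.1 / 19.2 |
| Skewness 1.75 (CV about 0.5) | 82.4 / 93.7 / 89.3 | 41.7 | 7.5 / 3.8 / 5.9 |

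With no group differences, the pooled check at CV 0.3 switches about 63%.

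**4. Is the gate itself at fault, or what lies behind it?** The rule was re-run with Shapiro-Wilk on residuals and a Kruskal-Wallis test in place of Friedman (6,000 runs per row). In the lognormal rows the same standardised shifts were applied on the log scale. All entries are per cent.

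| Data | Type I error, gated | Power, gated | Power, ANOVA alone |
|---|---|---|---|
| Normal | 5.4 | 80.9 | 80.8 |
| Lognormal CV 0.3 | 5.3 | 79.4 | 78.9 |
| Lognormal CV 0.5 | 4.4 | 78.8 | 77.3 |
| Lognormal CV 0.8 | 5.3 | 78.5 | 72.0 |
| Lognormal CV 1.2 | 4.8 | 78.2 | 62.1 |

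The Monte Carlo standard error near 5% is √(0.05 × 0.95/6,000) = 0.3 points. With a valid rank test the omnibus rule holds its error rate and loses no material power. ANOVA with no gate also stays near nominal type I error on lognormal data with CV 0.3 to 0.5 (4.7 to 5.5% across runs).

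**The case against.** The strongest reply is that the rule is prespecified and mechanical, is common practice, and that switching is not in itself harm. Much of this stands.

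- A reader might infer that the gate is damaging whichever rank test is named. Step 4 does not support that: with Kruskal-Wallis behind it, the omnibus rule behaves well.
- A reader might also infer that the gate protects nothing. That holds for ANOVA's type I error at moderate skew but not for power, where a valid rank test gains under heavy skew (78.5% v 72.0% at CV 0.8). The rule also covers secondary laboratory markers, where skew is plausible.
- The 46% figure needs checking by arm and 12 independent checks. The protocol states neither, and four strength and function tests in the same patients are unlikely to be independent.
- The skew results are assumptions. The trial is sized on percentage change, and skew in raw scores need not carry over to it.
- Which data are checked, and a post hoc test for the rank branch, are details an article may leave to a fuller plan. They are not counted as faults here.

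What does not yield is the stated text. The article names Friedman for the non-normal branch and makes ANOVA with Tukey conditional on passing the check. A fuller plan could add a pairwise procedure, but adding one to a related-samples test would not make it compare three independent arms. Even with a valid rank test, whether a primary outcome is reported as a mean difference would still depend on its data.

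**Conclusion.** The point holds for the rule as written: the normality gate combined with a Friedman branch. A primary outcome that fails the check gets no valid comparison of the three arms, no stated BFR-C v CYC comparison, and no estimate on the scale used for sizing.

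For exactly normal data the size is modest. About 5% of outcomes are affected (about 14% if checked by arm), so up to about 18.5% of trials lose at least one of four primary outcomes. The chance of reaching a significant BFR-C v CYC contrast falls by about 2 points, or about 6 if checked by arm. Under assumed skew of about 0.95, some 47 to 60% of outcomes switch and that chance roughly halves, from 40% to 18 to 21%. These figures assume 20 completers per arm and, for the skewed cases, lognormal errors.

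The documents do not support saying that the rule inflates type I error, that the analyst is free to choose a preferred result, or that the sample size is wrong for the omnibus test. The change should be made; it does not call the design into question.

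**What to change.** Remove the normality gate for the primary outcomes. Suitable wording would be: each primary outcome will be compared between the three groups by one prespecified linear model (one-way ANOVA or its baseline-adjusted form), whatever a normality test shows, and the BFR-C minus CYC difference will always be reported with its confidence interval.

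Replace Friedman with an independent-groups rank test, for example Kruskal-Wallis with pairwise comparisons, as a sensitivity analysis that cannot displace the primary result. If a rank route is kept for secondary variables, the same independent-groups test should be named there. Naming in advance a log transform for laboratory markers expected to be skewed is optional and not needed for this fix.

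The cost is a few sentences and one sensitivity table; 20 per group and 75 in total stand. The downside is that an unexpectedly skewed outcome is reported on the mean scale first. In step 4 this costs little power up to CV 0.5 (77.3% v 78.8%) but more if skew is heavy (62.1% v 78.2% at CV 1.2).

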## Methods

### Design

This is a 12-week randomised controlled trial consisting of three groups randomised to exercise or usual care (Fig. 1). Participants will be randomised to one of three groups: a blood flow restriction cycling exercise training group (BFR-C), a non-blood flow restriction cycling exercise training group (CYC), or a non-exercising, usual care control group (CON).

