### Randomisation

Randomisation will be conducted at a participant level prior to familiarisation and baseline testing, and will randomise participants by blocks of 4 via a computer-generated random number sequence by an independent researcher. Blinding of intervention group to clinical staff and participants will not be possible once the intervention commences.

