### Data collection

Data collection will occur at baseline (T_1_) and 12 weeks (T_2_), with testing to be completed at the treating HD unit prior to the commencement of the participants’ HD session. Personal information, including relevant medical history will be collected prior to the initiation of testing or intervention upon receiving participant consent. This will include patient characteristics of age, gender, time in months that the participant has been receiving HD (dialysis vintage), basic anthropometric measures (height, weight, and BMI), relevant comorbidities and medications, transplant status, and type of dialysis access. Some or all of which may be taken, with approval, from the case file at the HD unit. The remaining data collected will include all measures of muscle function and physical function. Body composition scans will be performed on a non-dialysis day, separate from other testing procedures for participants who opt-in to this aspect of testing. Additional pathology measurements will include haemoglobin, albumin, potassium, parathyroid hormone, phosphate, urea reduction ratio (URR), creatine kinase and lactate. These measures will occur as part of routine pathology tests where possible, or will be requested out-of-cycle to coincide with the necessary period of the training intervention. Data will be coded and stored securely at Deakin University. Data collected from those who withdraw from the study will not be used for statistical analyses. This has been accounted for when completing the power analysis, with an additional 20% added to the target sample size. Attrition may be for a number of reasons, which will be ascertained upon withdrawal where possible.

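### The fallback for non-normal outcomes is the Friedman test, which needs related observations and does not fit a comparison of three independent randomised arms

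*Protocol article*

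**What the plan says.** All places are in the Methods of the protocol article.

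- **Design:** "Participants will be randomised to one of three groups": blood flow restriction cycling (BFR-C), conventional cycling (CYC) and usual care (CON). No crossover is described.
- **Randomisation:** "Randomisation will be conducted at a participant level prior to familiarisation and baseline testing, and will randomise participants by blocks of 4". No matching of participants between arms is described.
- **Data collection:** outcomes are measured at two times, baseline (T1) and 12 weeks (T2). Data from participants who withdraw are left out of the analysis.
- **Statistical analysis, trigger:** "The distribution of data will be assessed for normality with a Shapiro-Wilks test".
- **Statistical analysis, fallback:** "Non-normally distributed data will be compared using the Friedman non-parametric test".
- **Statistical analysis, default:** "Otherwise, comparisons between groups for all continuous primary and secondary variables measured will be made using one-way analysis of variance (ANOVA", followed by Tukey comparisons.
- **Statistical analysis, participant characteristics:** these are to be "compared using independent t-tests for continuous variables and chi-square tests for categorical variables".

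**The concern.** The fallback and the default are presented as two routes to the same comparison, and the choice between them depends only on the normality test. The default is a test for independent groups. The fallback is a test for related samples. It ranks the values inside each block (for example, one person under several conditions) and asks whether one condition tends to rank higher. This trial has no block that contains one BFR-C, one CYC and one CON participant.

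The rule covers every continuous primary and secondary variable. For any outcome sent down this route, the prespecified test cannot be run as written, or gives a P value that depends on an arbitrary ordering of participants, or answers a question other than the difference between arms. The analyst would then have to choose a different test after seeing the data, which is what prespecification is meant to prevent.

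**Working it through.** **1. Which test the trial was sized for.** Inputs from the Sample size calculation section: mean changes of −3, 2 and 12, SD 15, α 0.05, 20 per group, 20% attrition.

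- Overall mean = (−3 + 2 + 12)/3 = 3.667. Squared deviations: 44.44 + 2.78 + 69.44 = 116.67.
- Cohen's f = √(116.67/3)/15 = 6.236/15 = 0.416.
- Noncentrality at 20 per group = 20 × 116.67/225 = 10.37, on 2 and 57 degrees of freedom.
- Power = 0.809 at 20 per group and 0.786 at 19, so 20 is the smallest size that reaches 80%.
- With attrition: 60/(1 − 0.20) = 75.

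Both stated figures reproduce. The trial is sized for a between-group one-way ANOVA, and the fallback has to answer the same question.

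**2. Friedman across arms: equal sizes.** The test needs one value per arm in every row. Equal allocation (25 per arm) is an assumption, since the article gives no ratio. Under it, blocks of 4 do not divide evenly among three arms. Withdrawals are then removed. If each participant withdraws independently with probability 0.20, the chance that all three arms end up the same size is Σₖ [C(25,k) 0.2ᵏ 0.8²⁵⁻ᵏ]³ = 0.023. When one arm was one participant short (20, 20, 19), the calculation returned an error.

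**3. Friedman across arms: dependence on row order.** One data set was simulated with the planning means and SD and 20 per arm, and its values were re-paired into rows 5,000 times.

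| Test, same data | P value |
|---|---|
| Kruskal-Wallis | 0.0014 |
| Friedman, full range over re-pairings | 0.00001 to 0.25 |
| Friedman, middle 95% of re-pairings | 0.0003 to 0.074 |

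Kruskal-Wallis gives one answer. Friedman gives as many as there are ways to order the rows.

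**4. Friedman across arms: power and type I error.** 3,000 simulated trials, normal data, planning means, SD 15, 20 per arm. Simulation standard error at 0.65 is √(0.65 × 0.35/3000) ≈ 0.009.

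| Test | Power |
|---|---|
| One-way ANOVA | 0.80 |
| Kruskal-Wallis | 0.77 |
| Friedman, arbitrary rows | 0.65 |

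With no difference between arms, Friedman rejected in 0.049 of trials.

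**5. Friedman across T1 and T2.** With two time points the test reduces to a sign test on each participant's change, and arm does not enter it. Suppose every arm has the same change, normal with mean 5 and SD 15, in 60 participants (an assumed example).

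- Chance that a participant improves = Φ(5/15) = 0.631.
- The test rejects when |2b − 60| > √(3.84 × 60) = 15.18, where b is the number who improve: b ≥ 38 or b ≤ 22.
- Rejection probability = 0.54.
- With no change over time, the same rule rejects with probability 0.052.

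The test is detecting the shared change over time. It says nothing about the arms.

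**6. Participant characteristics.** An independent t-test takes two groups, so three arms need three tests. At 0.05 each, the chance of at least one false positive is about 0.12 (simulated, 25 per arm); the formula for independent tests gives 1 − 0.95³ = 0.143. No outcome is involved.

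**The case against.** **The error is in a conditional fallback.** This stands. One-way ANOVA suits three independent groups, and the sample size matches it. How often the fallback would be used is unknown. Even for truly normal data the trigger rate depends on how Shapiro-Wilk is applied, which the article does not say: about 5% per outcome on pooled residuals, about 14% (1 − 0.95³) if each arm is tested separately.

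**Friedman may be meant for change within a group.** The wording is against this, because the following sentence offers ANOVA between groups as the other branch. Even if it were meant, step 5 shows that it would leave non-normal outcomes with no comparison between arms.

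**The randomisation blocks might serve as Friedman blocks.** They cannot do so in the ordinary test, which needs exactly one participant per arm in each block. A block of 4 cannot supply that for three arms, and excluding withdrawals leaves gaps.

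**The power figures come from normal data.** This is true, and the plan would send such data to ANOVA. The figures show the kind of loss to expect; they do not estimate it for the outcomes that would reach the fallback. The conclusion rests on the design.

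**Stronger readings that the documents do not support.**

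- A reader might infer that Friedman inflates false positives between arms. With equal arms and arbitrary rows, type I error is about nominal.
- A reader might take the 0.54 in step 5 as a false-positive rate. It is power to detect a real change over time.
- A reader might expect the sit-to-stand count and the timed up and go to be skewed and so certain to reach the fallback. The article reports only the reliability and validity of these tests.
- A reader might give the t-tests equal weight. They apply only to participant characteristics and demographics, and change no efficacy result.

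**Conclusion.** The Friedman sentence names the wrong test, and nothing else in the article corrects it. This is a method stated wrongly, so it cannot be put down to detail left for an unseen analysis plan. It should be corrected before analysis, because it could govern primary outcomes.

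The harms that the documents support are these: the test has no natural rows; it fails when arms are unequal, which is very likely if allocation is equal and withdrawals run near 20%; its P value depends on row order; and it loses power, by about 0.12 against Kruskal-Wallis in the illustrative simulation (0.77 − 0.65). Used across visits, it does not compare the arms at all.

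The finding does not extend to the default ANOVA or to the sample size, both of which are consistent with the three-arm design. The t-tests are a minor point.

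**What to change.** Replace the Friedman sentence with one saying that non-normally distributed outcomes will be compared between the three groups by the Kruskal-Wallis test, on the same variable that the ANOVA would use, followed by a matching post hoc procedure such as Dunn's test with adjustment for multiplicity.

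As a minor edit, drop the t-tests and chi-square tests on participant characteristics and describe baseline by arm. Differences at baseline between randomised arms are due to chance, so description is enough.

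The cost is one or two sentences in the analysis section. No change is needed to data collection, sample size or the default analysis.

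### The planned one-way ANOVA does not name the analysed quantity and makes no baseline adjustment; ANCOVA on the 12-week value would settle the first and gain power at no cost

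*Protocol article*

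**What the plan says.** All places are in the protocol article, under Methods.

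- **Statistical analysis.** For data judged normally distributed, "comparisons between groups for all continuous primary and secondary variables measured will be made using one-way analysis of variance (ANOVA"). Tukey's test follows. The section mentions no covariate, change score or time factor.
- **Data collection.** There are two time points: "Data collection will occur at baseline (T_1_) and 12 weeks (T_2").
- **Sample size calculation.** The calculation uses "the projected percentage changes in knee extensor muscle strength for each of the three groups", namely "CON = −3%, CYC = 2%, BFR-C = 12" per cent. On spread: "The common standard deviation within group, based on the prior research was determined to be 15". The target is to "detect a difference between the expected means for percentage strength improvement", and "to achieve a power of 80% at an α level of 0.05, 20 participants per group will be required". Attrition of 20% brings the total to 75.

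**The concern.** One-way ANOVA can be run on the 12-week value or on the change from baseline, and the section does not choose. The choice matters for two reasons.

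- The SD of 15 belongs to percentage change. A 12-week value varies with the whole spread between patients, which may be much larger. Power could then fall well below plan.
- Neither version uses the baseline as well as it could. A 12-week comparison discards it. A change score subtracts all of it, whatever the correlation. Adjustment by regression removes only the part that predicts the outcome.

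The contrast most exposed is BFR-C versus CYC. It is the hypothesis stated at the end of the Background, and the projected difference is only 12 − 2 = 10 points. Leaving the analysed quantity open also allows it to be settled after the data are seen.

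**Working it through.** **Inputs from the Sample size calculation.** Means −3, 2 and 12; SD 15, read as percentage points of change; alpha 0.05; 20 evaluable per group.

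**Assumptions, not in the document.** The baseline to 12-week correlation r is taken from 0.3 to 0.9. The SD is taken as equal at both times. Percentage change is treated as a simple difference, which is an approximation.

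**Step 1: reproduce the plan.** The grand mean is 11/3 = 3.67. The sum of squared deviations is (−6.67)² + (−1.67)² + (8.33)² = 116.67. The noncentrality is λ = n × 116.67 / SD².

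- n = 19: λ = 9.85, power 78.6%.
- n = 20: λ = 20 × 116.67 / 225 = 10.37, power 80.9% (F with 2 and 57 df).
- Attrition: 60 / (1 − 0.20) = 75.

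The plan's figures therefore reproduce for a one-way ANOVA with percentage change as the analysed variable.

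**Step 2: pairwise power on change.** For BFR-C versus CYC the noncentrality is 10 / (15 × √(2/20)) = 2.11. Against the Tukey critical value of 2.41 (57 df), power is about 39%. An unadjusted t-test would give 54%, but that is not the planned test.

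**Step 3: the other two analyses.** Hold the SD of change at 15.

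- SD of the 12-week value: s = 15 / √(2(1 − r)).
- ANCOVA residual SD: s√(1 − r²) = 15√((1 + r)/2), with one error df fewer. This leaves out the small variance cost of chance baseline differences between arms, so the ANCOVA figures are slightly generous.

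| r | SD, 12-week | Omnibus, 12-week ANOVA | Omnibus, change ANOVA | SD, ANCOVA | Omnibus, ANCOVA |
|---|---|---|---|---|---|
| 0.3 | 12.7 | 92.4% | 80.9% | 12.1 | 94.6% |
| 0.5 | 15.0 | 80.9% | 80.9% | 13.0 | 91.0% |
| 0.6 | 16.8 | 71.0% | 80.9% | 13.4 | 89.1% |
| 0.7 | 19.4 | 57.7% | 80.9% | 13.8 | 87.0% |
| 0.8 | 23.7 | 41.0% | 80.9% | 14.2 | 85.0% |
| 0.9 | 33.5 | 22.3% | 80.9% | 14.6 | 82.9% |

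BFR-C versus CYC with the Tukey critical value:

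| r | 12-week ANOVA | Change ANOVA | ANCOVA |
|---|---|---|---|
| 0.3 | 54% | 39% | 58% |
| 0.5 | 39% | 39% | 51% |
| 0.6 | 31% | 39% | 48% |
| 0.7 | 23% | 39% | 46% |
| 0.8 | 15% | 39% | 43% |
| 0.9 | 8% | 39% | 41% |

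The break-even for 12-week values is r = 0.5, where s = 15. ANCOVA is ahead of both alternatives at every r examined.

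**The case against.** The strongest reply is that the two sections should be read together. The sample size reproduces when the stated test is applied to percentage change, so ANOVA on change is probably what was meant. On that reading baseline is used, planned power holds, and ANCOVA adds only about 2 omnibus points at r = 0.9 and 8 at r = 0.6. The article is condensed, and the definition of the analysed variable may sit in a fuller plan.

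Most of this stands, and it limits the point. A reader might infer that the trial ignores baseline altogether, or that the analysis contradicts the sample size. The document supports neither inference: the Statistical analysis section leaves the quantity open, and one natural reading agrees with the sample size. A reader might also take the 22% figure as the trial's power. It arises only if 12-week values are analysed and r is 0.9. At r of 0.5 or below, that analysis meets or exceeds plan. Nor does chance baseline imbalance bias the ANOVA under randomisation; it costs precision.

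What the reply does not remove is that the article fixes a test for every continuous outcome, and that test is unadjusted on either reading. The Physical function section gives reliability coefficients of 0.91 to 0.96 for the three function tests in dialysis patients. They are not 12-week correlations, which may well be lower, but they make a high r plausible for those outcomes, and a high r is where a 12-week-only comparison loses most.

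**Conclusion.** The point holds as an ambiguity plus an avoidable loss of efficiency. It is not an error in the sample size, which is correct for ANOVA on percentage change.

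- **If change is analysed:** omnibus power is about 81% as planned. ANCOVA gives 83% (r = 0.9) to 95% (r = 0.3), and BFR-C versus CYC under Tukey rises from about 39% to 41%–58%.
- **If 12-week values are analysed:** omnibus power falls from 92% to 22% as r goes from 0.3 to 0.9, below plan only when r exceeds 0.5.

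The large loss and the large gain over change scores do not occur together: at high r, change scores are already nearly as good as ANCOVA. The sizes depend on the assumed r and on the SD conversion. The ranking of ANCOVA first does not depend on r within the range examined. Even with ANCOVA, BFR-C versus CYC stays well below 80%, so the change helps that contrast without rescuing it.

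**What to change.** In the Statistical analysis section, state that each continuous outcome is analysed by ANCOVA of the 12-week value on arm, with the baseline value of the same outcome as covariate. For strength, use the log scale if a percentage effect is wanted, so that the result keeps the percentage terms of the sample size. Keep a Tukey-type multiplicity adjustment for the pairwise contrasts, and report adjusted differences with 95% confidence intervals, BFR-C versus CYC first. Use the same model for continuous secondary outcomes measured at both times.

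The cost is wording. No extra data or participants are needed, and the target of 75 can stand. One caution: the Randomisation section places allocation before baseline testing. The covariate is cleaner if it is measured before allocation is known, but change scores depend on the same baseline, so this is no reason to prefer them.
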